Note that all subjects will have the option to decline home testing and wait until research operations resume and they can complete the blood draw per the usual protocol. Subjects who choose to wait will also be compensated \$20 for completing the blood draw *only* for survey data collection visits completed during the COVID-19 pandemic. Once research operations

resume, subjects will be paid as outlined in section 6.2 *Transition and Retention*.

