### **Transition and Retention**

Despite having "access" to healthcare, participants will be economically vulnerable individuals with uncontrolled diabetes. Ethically, we acknowledge that the "usual care" currently received often does not meet patients' needs or standards of care. Therefore, participants assigned to usual care will receive initial support to engage existing resources available through UI Health, such that healthcare providers will consider this an acceptable alternative upon randomization (clinical equipoise).

Upon randomization, participants will receive referrals to a diabetes educator and clinical pharmacist for medication reconciliation, adherence support, and education. Staff can schedule the visit at data collection. This is important as our prior work with medication reconciliation identified discrepancies in almost 60% of patients. A one-page list of clinic resources with names and direct telephone numbers (e.g., social worker) will be provided so they can more easily navigate the system. Finally, low-literacy, paper-based diabetes education information will be provided. At the end of year 1, these patients will cross-over and receive *mDAS*. Prior to this transition, HCs will work with the patients and their social support network to prepare them for the transition. Participants randomized to usual care will receive *mDAS* for one year.

*Retention strategies.* Participants will be reimbursed \$30 for each data collection. Participants assigned to the intervention in year one will receive an additional \$50 at 6 months and 12 months if they complete at least one videoconference before each data collection. Participants assigned to the intervention in year two will receive an additional \$50 at 18 months and 24 months if they complete at least one videoconference before each data collection. Participants who complete all five data collection visits and videoconferences with the pharmacist as described above will receive up to \$250 for completing the study.

*Additional Retention Strategies for mDAS Sleep Sub-study Supplement* Participants will be reimbursed an additional \$40 for participating in the sleep sub-study and turning in the wrist actigraph.

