### **Primary Outcomes**

Univariate comparisons between the two study groups for outcomes and covariates at baseline will be conducted using chi-square tests for categorical variables, Kruskal-Wallis tests for ordinal variables, and t-tests for continuous variables. Non-normal continuous data will be transformed prior to analysis.

In order to provide comprehensive analysis for  $H_1$ , we will extend the usual analysis of crossover designs by including a longitudinal trend component in the first year. Thus, we can examine the time course (0, 6, and 12 months) as linear or quadratic over the first three

measurements. This will allow us to investigate whether changes are made early, and at what rate they continue through the rest of the time period. This analysis permits the comparison of trends between the two conditions. In addition, we will regard subjects as a random effect and will use Gaussian mixed-model estimation (SPSS MIXED). We can then substitute treatment by period interactions for the carry-over effects, and the model can be reduced in a recommended sequence (first omit carry-over, then omit treatment, finally omit period). SPSS MIXED will also be used to explore patterned covariance structures such as compound symmetry and autoregression along with incorporating time-constant and time-varying covariates, such as health literacy or diabetes distress.

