### Sustainability

We expect a limited amount of decline in physiologic outcomes with the transition back to usual care. We will test the hypothesis that improvements in A1c, blood pressure, and LDL cholesterol will be maintained during the maintenance time period. The analyses will be conducted similarly as for H1, and will evaluate change in the initial intervention group one year after intervention completion.

Consulting with [name], we will implement a *Sustainability Action Plan (SAP)* to integrate HCs and ensure provision of pharmacy telehealth at an organizational level beyond the period of grant funding. The first phase will identify existing organizational goals and activities that support integration of HCs and pharmacy telehealth approaches into routine clinical operations. Our healthcare system is actively testing HC/peer educator models in multiple locations of the network. In collaboration with these sites and other key stakeholders, we will adapt an existing sustainability checklist to evaluate the presence of specific factors that are needed to support on-going operations within the organization. The next phase involves identifying existing and needed resources within our organization to support delivery of the additional services at the end of the study. The cost-effectiveness data (Aim 3) will help guide this procedure. Working with the Illinois Healthcare Reform Implementation Council and our existing relationship with the Illinois Community Health Worker Advisory Board (see letter of support), we will share details on training and reimbursement for community health workers (aka health coaches) as set forth in the Affordable Care Act and Illinois Bill HB5412 (the board will propose training and certification processes for community health workers and advice legislators). [name] (consultant), as the Global Director of Peers for Progress, is actively involved in legislation to provide peer support service reimbursement and will aid in identifying relevant stakeholders. The final step focuses on executing the outlined action plan.

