Sample Size Justification: Sample size calculations are powered to detect change in A1c. The ADA Technical Review of Diabetes Self-Management Education reported that successful education programs achieved reductions of 5-20% in A1c. The UKPDS 35 demonstrated that each 1% absolute reduction in mean A1c is associated with a 21% decrease in risk for any diabetes-related endpoint, a 21% decrease in diabetes-related deaths, a 14% decrease in risk for myocardial infarctions, and a 37% decrease in risk for microvascular complications. Based on our previous studies, we estimated a mean baseline A1c level of 10% with standard deviation of 1.8 and an effect size of  $(1.0/1.8) 0.56$  for Aim 1. The cross-time correlation was estimated to be 0.30 with compound symmetry structure. We adjusted for clustering and assumed an intraclass correlation coefficient (ICC) of 0.01 with five clusters. This yielded a design effect of 1.34. Two-sided alpha of 0.05 and 80% power were assumed. Allowing for 20% drop-out, 220 patients will be required total.

UI Health billing data show there are 7,258 adult African-Americans and Latinos with diabetes. We estimate that approximately half of these patients have an A1c level above 8.0% based on prior study. We anticipate recruiting 6% of the eligible diabetic population. We have successfully recruited a similar size of patients with type 2 diabetes using comparable recruitment methods.

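### The Aim 1 crossover model may be reduced by dropping carry-over first, although Aim 2 expects the Year 1 gain to persist; if carry-over is dropped, the mDAS effect estimate shrinks by up to half

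*Protocol*

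**What the plan says.** Section 12.0, Primary Outcomes, analyses H1 by extending the standard crossover analysis. Treatment-by-period interactions stand in for carry-over, and the text adds that "the model can be reduced in a recommended sequence (first omit carry-over, then omit treatment, finally omit period". The same paragraph adds a trend component over months 0, 6 and 12 that allows the two conditions to be compared within Year 1. The next paragraph gives the label of primary analysis to a joint repeated-measures analysis of all physiological outcomes.

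Section 12.0, Sustainability, expects only limited decline after the return to usual care and states: "We will test the hypothesis that improvements in A1c, blood pressure, and LDL cholesterol will be maintained during the maintenance time period". Section 6.1, Crossover Transition, phases mDAS out at one year so that maintenance can be assessed. No washout is described. In Year 2 the mDAS-first group is therefore on usual care while the usual-care-first group receives mDAS.

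**The concern.** Leaving carry-over out of a two-period crossover is safe only if the first-period effect has gone by the time the second period is measured. Here persistence is the Aim 2 hypothesis, so one part of section 12.0 allows the removal of the very effect that another part sets out to find.

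Without the carry-over term, Year 2 compares patients now on mDAS with patients who may still hold their mDAS gain. That smaller difference is averaged with the valid Year 1 difference. The estimate is pulled towards zero most strongly when the intervention works and its effect lasts. If the choice of model depends on the data, the reported interval also loses its nominal coverage.

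**Working it through.** **Inputs** (Sample Size Justification, section 12.0)

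- Variability and effect: "mean baseline A1c level of 10% with standard deviation of 1.8 and an effect size of" 1.0/1.8 = 0.56, so the planned effect is tau = 1.0 point.
- Correlation: "The cross-time correlation was estimated to be 0.30 with compound symmetry structure".
- Error rates: "Two-sided alpha of 0.05 and 80% power were assumed".
- Clustering: "assumed an intraclass correlation coefficient (ICC) of 0.01 with five clusters", with a stated design effect of 1.34.
- Size: 220 patients with 20% drop-out gives 176 completers. I assume 1:1 allocation (no ratio is stated), so 88 per arm.
- c, the share of the effect maintained in Year 2: not given, so I take the range 0 to 1.

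**The plan's own figures.** The design effect reproduces: 1 + (176/5 - 1) x 0.01 = 1.342. The 220 does not reproduce directly, because the test behind it is not stated. Comparing final values needs 51 per arm, 137 in total after the design effect and 172 after drop-out. Comparing change scores gives totals of 143, 191 and 239 at the same stages. These bracket 220, and nothing below depends on it.

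**Estimate with carry-over omitted.** The Year 1 benefit (mDAS-first against usual-care-first) is tau. The Year 2 benefit (usual-care-first, now on mDAS, against mDAS-first) is tau - c x tau. The reduced model averages the two:

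estimate = 0.5 x [tau + tau(1 - c)] = tau(1 - c/2)

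| c | Estimate for tau = 1.0 |
|---|---|
| 0 | 1.00 |
| 0.25 | 0.875 |
| 0.5 | 0.75 |
| 0.75 | 0.625 |
| 1 | 0.50 |

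Generalised least squares under compound symmetry gives the same values at c = 0, 0.5, 0.75 and 1 for visits at 12/24, 0/12/24 and 0/6/12/18/24 months. This takes the full effect as present at both visits of the active year and carry-over as constant in Year 2.

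**Standard errors, 12- and 24-month values**

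- Reduced crossover estimate: 0.5 x sqrt(4 x 1.8² x 0.7/88) = 0.161
- Year 1 difference: 1.8 x sqrt(2/88) = 0.271
- Carry-over: sqrt(4 x 1.8² x 1.3/88) = 0.438

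With the design effect each is multiplied by sqrt(1.34), giving 0.186, 0.314 and 0.507.

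If carry-over is always omitted, 95% interval coverage is 66% at c = 0.5 and 12% at c = 1 (73% and 23% with the design effect).

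**If omission depends on a two-sided 5% test (assumed).** At c = 1 the expected z is 1/0.438 = 2.29, so carry-over is missed in 37% of trials. At c = 0.5 z is 1.14 and it is missed in 79%. Using all five planned visits lowers the miss rates. Simulated results of test-then-choose:

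| Data used | c | Carry-over missed | Mean estimate | Coverage |
|---|---|---|---|---|
| 12, 24 months | 0.5 | 79% | 0.86 | 70% |
| 12, 24 months | 0.75 | 60% | 0.86 | 59% |
| 12, 24 months | 1 | 37% | 0.90 | 65% |
| Five visits | 0.5 | 68% | 0.89 | 57% |
| Five visits | 1 | 16% | 0.96 | 82% |

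The average cut over c = 0.5 to 1 is thus about 10 to 14% with two visits and 4 to 11% with five. With the design effect these become 15 to 17% and 7 to 13%. The average hides two wrong answers: 0.50 when carry-over is dropped at c = 1, and about 1.13 when it is kept because the test was significant (two visits).

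**Power.** At c = 1 the reduced two-visit model still has 88% power (77% with the design effect). The Year 1 difference in final values has 96% (89%).

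**The case against.** The wording is permissive. It says the model can be reduced and names no test, no threshold and no commitment to omit carry-over. A reader might infer that the plan fixes a biased estimator and that the effect will be halved. The text does not support that: halving needs both full maintenance and actual omission, and the protocol itself expects some decline. If carry-over is kept, the Year 1 contrast is recovered. This part of the objection stands, and it is why the size is stated conditionally.

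The Year 1 trend component is a valid comparison, and another analysis is called primary, so the crossover model is not the only one described. That also stands. Yet neither paragraph makes the Year 1 contrast the Aim 1 estimate or exempts it from the reduction, so which number answers Aim 1 is left open.

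A reader might also infer that the 12-month comparison is contaminated by other routes. The COVID-19 text says "all subjects will have the option to decline home testing and wait until research operations resume", and Transition and Retention says "Prior to this transition, HCs will work with the patients and their social support network to prepare them for the transition". Neither supports a finding. No passage says that mDAS starts before a deferred 12-month draw, and the protocol gives no number or length of deferrals. The transition sentence gives no timing or amount of contact before the 12-month visit and may be loose drafting.

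**Conclusion.** The point holds in conditional form and should be fixed. Section 12.0 allows carry-over to be dropped from the Aim 1 model while expecting the effect to persist. If it is dropped, the estimate is tau(1 - c/2): a cut of a quarter at half maintenance and of half at full maintenance. Under an assumed 5% test the average cut for c from 0.5 to 1 is about 4 to 14% (7 to 17% with the design effect), with interval coverage of about 57 to 82% before the design effect.

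These figures rest on the plan's SD, correlation and drop-out, 1:1 allocation, a full effect at both active-year visits and constant carry-over. The harm is to the size of the effect and its interval. The trial's ability to detect an effect is not mainly at risk.

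**What to change.** In section 12.0, Primary Outcomes:

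- Delete the reduction sequence and any test of carry-over.
- State that Aim 1 is estimated as the randomised mDAS versus usual-care difference at 12 months, from Year 1 data only (0, 6 and 12 months).
- State that Year 2 data serve Aim 2 and are otherwise descriptive.

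The cost is wording. Year 2 no longer adds apparent precision to Aim 1: the standard error is 0.271 instead of 0.161 on final values, but the smaller figure belongs to an estimate that is unbiased only if c = 0. Power for Year 1 final values remains about 96% (89% with the design effect). An analysis of simple change scores would be weaker, at 88% (77%), so the Aim 1 sentence should also say how baseline enters the model.

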### **6.1 Overview of Participant Procedures**

#### Recruitment and Randomization

1. Potential participants will be identified by one of four recruitment methods previously described.
2. RAs will screen patients for eligibility and discuss the study protocol in detail. If the patient is deemed eligible to participate he/she will complete written informed consent and HIPAA authorization.

3. Enrolled participants will schedule an appointment at the UIC Clinical Interface Core (CIC) to complete baseline data collection, which includes a blood draw.
4. Participants randomized to *mDAS* will receive the intervention component in Year 1, while participants randomized to *Usual Care* will receive it in Year 2. RAs will inform participants of assignment.

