#### Usual Care Component

1. Participants will receive contact information for a diabetes educator and a clinical pharmacist for medication reconciliation.
2. Patients will receive a one-page contact sheet with the names and phone numbers of their local healthcare team as well as paper-based, low-literacy diabetes educational information.

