#### mDAS - Pharmacist Component

1. Pharmacists will provide medication and disease management services to patients by following a Pharmacist Management Protocol (see attached).
2. The initial pharmacist videoconference will include medication reconciliation and review therapeutic goals.
3. Follow up videoconferences will occur every other month. The interval duration may increase/decrease based on individual preference and when subjects reach goals.
4. These subsequent visits will involve an evaluation of adherence, medication reconciliation, and a review of home glucose and/or blood pressure monitoring data, an evaluation of drug interactions and side effects, goal setting, basic lifestyle

modifications, pillbox use, development of a low-literacy medication list, and other adherence aids.

5. Pharmacists will adjust therapy according to the plan of care under PCP guidance and notify PCPs of agreed upon modifications through EMR notifications. Side effects will be conveyed to the PCP (if the PCP is not available, the covering physician will be contacted as per Pharmacist management Protocol).
6. Pharmacists will forward all electronic progress notes to PCP EMR "Inbox" after each encounter.
7. If the PCP feels that the patient should not remain in the study the provider can inform the Co-PIs to disenroll the participant.

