If the intervention is effective, we will examine whether changes in self-efficacy, health beliefs, or social support serve as mediators for improved outcomes according to our conceptual framework. In addition, we will explore diabetes-related behaviors as well as medication treatment intensification as mediators using MPlus. To further identify the relative contributions of videoconferencing and/or text messaging, we will conduct mediational modeling with videoconferencing time, number of text messages, and HC contact time as mediating variables. This may describe any dose-response relationships between mHealth utilization and outcomes. We will compute bias-corrected bootstrap standard errors using MPlus. This offers accurate confidence intervals for mediation coefficients. Due to anticipated relationships between HC activity level and mHealth delivery, we plan to inspect correlations between mediators and incorporate any significant findings in model development. This analysis will demonstrate whether intervention effects are sensitive to mediators. Finally, given the sample size, observed (rather than latent) variables will be used in the mediation models. To enhance the power of mediation modeling, we will adopt an  $\alpha=.10$  Type I error criterion to improve the chances of finding promising mediators for future study.

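### The dose variables entered as mediators (videoconference time, text count, coach contact time) yield only a non-randomised slope within mDAS, so the models cannot apportion the effect between components

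*Protocol*

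**What the plan says.** Section 12.0, under Primary Outcomes, sets out mediation models to be run if the intervention works. One group of mediators is self-efficacy, health beliefs, social support, behaviours and treatment intensification. A second group is introduced by "To further identify the relative contributions of videoconferencing and/or text messaging", and for it "we will conduct mediational modeling with videoconferencing time, number of text messages, and HC contact time as mediating variables". The text continues: "This may describe any dose-response relationships between mHealth utilization and outcomes". It concludes: "This analysis will demonstrate whether intervention effects are sensitive to mediators". Intervals come from a bias-corrected bootstrap, correlations between mediators will be inspected, and the Type I error level is 0.10.

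On exposure, Section 6.1 gives mDAS to the intervention arm in Year 1, "while participants randomized to *Usual Care* will receive it in Year 2". Under the Usual Care Component, "Participants will receive contact information for a diabetes educator and a clinical pharmacist for medication reconciliation", together with a contact sheet and paper education. On dose within mDAS, the pharmacist component says of the follow-up videoconferences: "The interval duration may increase/decrease based on individual preference and when subjects reach goals".

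**The concern.** A mediation analysis multiplies two paths: arm to mediator, and mediator to outcome given arm. Randomisation protects the first. It never protects the second, but when the mediator varies in both arms, both at least contribute to estimating it. Here the first path is only the mean amount of intervention delivered, and the second comes almost entirely from comparing mDAS patients who took more with those who took less.

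Anything that drives both uptake and A1c then appears as an effect of the component. The planned conclusion, a division of the effect between videoconferencing, texting and coaching, would rest on that comparison while being presented as part of the trial's randomised evidence.

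**Working it through.** **1. Inputs from the protocol.** No stated figure is in dispute; the sample-size section only sets the scale. The A1c effect is 1.0 with SD 1.8 (1.0/1.8 = 0.56). Of 220 patients with 20% drop-out, 220 × 0.8 = 176 remain, or 88 per arm if allocation is equal (an assumption).

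**2. Exposure in usual care.** In Year 1 this arm has no study videoconferences, coaching programme or intervention texts. There are two small exceptions. Before crossover, "HCs will work with the patients and their social support network to prepare them for the transition" (Transition and Retention), and sleep sub-study participants in either arm may receive diary texts.

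**3. What the mediator coefficient estimates.** Regress outcome Y on arm and mediator M. The coefficient of M pools the two within-arm slopes, weighted by the within-arm sums of squares of M:

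b = (SS_UC × b_UC + SS_mDAS × b_mDAS) / (SS_UC + SS_mDAS).

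If M = 0 throughout usual care, SS_UC = 0 and b = b_mDAS exactly. Simulation confirmed this (largest difference 3 × 10⁻¹⁵). With the small exceptions above it holds approximately.

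**4. What determines dose within mDAS.**
- Videoconference frequency changes with preference and on reaching goals (pharmacist component).
- Patients may decline videoconferencing and stay in the study with coaching only (Pharmacy Management Protocol, A).
- Follow-up visits focused on medication changes may be cancelled when the patient has no glucose readings (same document, B).
- Replying STOP ends the texts (Section 7.0).
- Extra messages go to patients who miss their goals (Section 6.4, Text Messaging).

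Refusal, missing readings and STOP replies tend to link low dose to low engagement. The extra messages link high dose to poor progress. The goal-based interval makes dose partly a consequence of the outcome.

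**5. Size of the bias.** Suppose the component truly does nothing. Let engagement correlate r with better A1c and ρ with dose, and let CV be the dose SD divided by its mean m. Then

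b_mDAS = −ρ × r × 1.8 / (CV × m), and the indirect effect is m × b_mDAS = −1.8 × ρ × r / CV.

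Assume dose has mean 180 and SD √(90² + 60²) = 108.2, floored at zero. Before flooring, CV = 108.2/180 = 0.60. If 90 of that spread is engagement, ρ = 90/108.2 = 0.83. Lower ρ is also shown, with the same mean and spread.

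| ρ | formula, r = 0.1 / 0.2 / 0.3 | simulated spurious part of 1.0 point | significant at 0.10 |
|---|---|---|---|
| 0.3 | 0.09 / 0.18 / 0.27 | 0.09 / 0.19 / 0.28 | 11% / 15% / 21% |
| 0.5 | 0.15 / 0.30 / 0.45 | 0.15 / 0.31 / 0.46 | 12% / 24% / 40% |
| 0.83 | 0.25 / 0.50 / 0.75 | 0.26 / 0.53 / 0.78 | 19% / 45% / 76% |

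The simulated values run slightly above the formula because flooring trims the relative spread. With r = 0 the detection rate is about 10%, as it should be.

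**6. Direction and remedy.** A second set of runs used CV 0.5, ρ of 0.3 to 0.5 and r of 0.2 to 0.5. It gave a spurious indirect effect of −0.21 to −0.91. Reversing the sign of ρ, as when dose rises with poor progress, gave +0.21 to +0.90, which would mask a real contribution. Adjusting for engagement itself (ρ = 0.5, r = 0.3) gave an indirect effect of 0.00 and detection of 9.7%.

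**The case against.** The strongest defence is that this is declared screening. The models run only if the intervention works, the dose-response sentence is tentative, and the 0.10 level is openly justified as a search for mediators worth later study. A covariate list for mediation models commonly sits in the SAP, which is not at hand, and Section 12.0 does plan covariates for selection bias. These points stand and keep the matter away from the primary result. They do not rescue the stated purpose. The Section 12.0 covariates relate to study participation, not to uptake within mDAS. Inspecting correlations between mediators does not address confounding of mediator and outcome. The bootstrap deals with sampling error alone.

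Several stronger readings are tempting but unsupported:
- That the models must over-credit technology. The protocol's own dose rules can push either way, and coach contact is not a technology.
- That 0.78 is the expected size. It needs dose and engagement to correlate at about 0.83; no engagement figure is in the documents.
- That the result would decide which component is kept. The Sustainability text cites organisational factors and the Aim 3 cost-effectiveness data, not mediation.
- That exposure is exactly zero in usual care throughout. It is near zero, and in Year 1 only. In Year 2 that group receives mDAS, but its dose is again not randomised.
- That the three mediators have been shown numerically inseparable. The calculation uses one mediator, and the protocol already expects overlap with coach activity.

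**Conclusion.** The point holds as a limit on what this secondary analysis can claim. That the Year 1 mediator-outcome path is essentially the within-mDAS slope follows from the design and needs no assumption beyond near-zero exposure in usual care. That dose is self-selected and partly driven by progress follows from the protocol's own rules. The model therefore cannot deliver the purpose in "To further identify the relative contributions of videoconferencing and/or text messaging" or, for these three variables, the conclusion in "This analysis will demonstrate whether intervention effects are sensitive to mediators".

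The size is conditional. For a component with no effect, the spurious part of a 1.0-point effect runs from about 0.09 to 0.78, and false detection from about 11% to 76% against a nominal 10%. This rests on 88 per arm, SD 1.8, the assumed dose spread, r of 0.1 to 0.3 and ρ of 0.3 to 0.83. The sign may be reversed. The primary comparison and the sample size are unaffected.

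**What to change.** In Section 12.0, Primary Outcomes:
- Report videoconference time, text count and coach contact time as an exploratory, observational dose-response within mDAS.
- Adjust for baseline predictors of uptake already collected: A1c, medication adherence, health literacy and depression.
- Add a sensitivity analysis for unmeasured confounding between dose and outcome, since these covariates will capture engagement only in part.
- Delete the clause about identifying relative contributions, and soften the claim of demonstration for these variables.
- Give the same observational label to the comparison above and below median videoconferencing and text activity.
- Keep the mediators measurable in both arms (self-efficacy, beliefs, social support, behaviours, intensification), with the caution that they are not randomised either.

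The cost is a weaker claim and a little more analysis. No new data are needed.
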